### Impact research: The household survey

Using questionnaires that are designed to replicate the national 2014 Demographic Health Health Survey, CHPS+ will conduct baseline and endline demographic surveys for assessing impact. The baseline CHPS+ project survey sample is designed to obtain information to detect a 15% reduction in under-five mortality with 80% power at 5% level of significance in each of the two study regions. Overall, the interventions are taking place in eight districts (four in each region) while another eight districts (four in each region) are being used as comparison districts. Survey sampling is designed to draw a representative sample of the number of women of reproductive age (15–49 years) in three of the four treatment districts in each region and in four randomly selected comparison districts. Thus, a total of fourteen districts, seven per region, were included in the baseline survey. A two-stage stratified cluster sampling approach was used. In the first-stage, census enumeration area clusters were sampled, and in the second-stage, households will be sampled from the first-stage clusters. Because a minimum of 30 clusters is conventional for the first stage of cluster sampled household surveys [41], a relatively conservative starting point of 40 clusters each for intervention and control districts in each region was selected.

Because the sample is designed to detect separate under-five mortality effects in each of two regions, sample size calculations were completed independently for each region. Final sample size and sampling parameters were based on region-specific estimates of census enumeration area intra-cluster correlation (ICC) and the number of children under five expected per woman. These parameters were calculated from publicly available data from the 2014 Ghana Demographic and Health Survey [42]. In Volta Region, ICC was higher and the number of children expected per woman was lower than in Northern Region. Therefore, a larger number of clusters and a larger number of households per cluster will be sampled in Volta Region. Sampling requirements for each region were calculated using a software system for conducting power calculations in multi-level randomized experiments known as Optimal Design [43].

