#### Sample design

The sampling frame for the first stage was from the 2010 Population and Housing Census which provided a complete listing of Enumeration areas in the fourteen districts to be surveyed. The sampling frame contained information such as the location and estimated number of households. In each region, Enumeration areas were stratified by rural versus urban and by the estimated number of households in the cluster. Clusters were stratified into three groups (small, medium, or large yielding a total of 6 strata in each district. Enumeration areas were sampled from each stratum using probability proportional to population size (PPS). Weights will be applied at the cluster level to standardize probabilities of household selection based on the relative population size of clusters.

To obtain a sampling frame for the second-stage sampling, a household listing of all households in each cluster was compiled based on census information on household size and number women of reproductive age (15–49) in each household. Households were then stratified into three strata defined by the number of eligible women in each household.

To maximize sample efficiency for difference-in-difference estimation at the endline, baseline sample clusters will be reused without modification to permit longitudinal observation of clusters and the assessment of the average treatment effect arising from the timing of exposure of clusters to project interventions. The second-stage sampling procedure will be repeated, yielding a household sample for the longitudinal observation of children exposed versus unexposed to interventions over the duration of the project, with provision for statistical adjustment of baseline and endline differentials and changes in project endpoints that are unrelated to CHPS+ interventions.

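### The 80% power claimed per region rests on enumeration-area clustering alone, although intervention is by district (3 v 4 surveyed per region), so the figure is not supported at the level of allocation

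*Protocol article*

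**What the plan says.** The section on the household survey (Impact research) sets the target: "detect a 15% reduction in under-five mortality with 80% power at 5% level of significance in each of the two study regions". It adds that the two regions were sized independently because separate effects are wanted in each.

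On the basis of the calculation it says: "Final sample size and sampling parameters were based on region-specific estimates of census enumeration area intra-cluster correlation (ICC"), together with the expected number of under-fives per woman. The tool was "a software system for conducting power calculations in multi-level randomized experiments known as Optimal Design", and the calculation began from this: "a relatively conservative starting point of 40 clusters each for intervention and control districts in each region was selected". The final survey has 247 enumeration areas in 14 districts (Hypotheses and goals).

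The same section describes allocation by district, with four intervention and four comparison districts per region. Women are sampled "in three of the four treatment districts in each region and in four randomly selected comparison districts", which makes seven surveyed districts per region. The section on systems learning districts places the intervention on the district management system.

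Under Assessing impact, the effect is the treatment-by-period interaction in equation (1). That model has residuals for cluster and individual only. Sample design reuses the baseline enumeration areas at endline with a new household sample: "To maximize sample efficiency for difference-in-difference estimation at the endline".

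**The concern.** Power has to be computed at the level where treatment is allocated. If districts receive the programme, all enumeration areas in a district share its mortality trend: its epidemics, harvests, staffing and other programmes. Differencing over time removes stable differences between districts, but not differences in how districts change. With 3 districts against 4, that variation enters the regional estimate with weight 1/3 + 1/4, and adding enumeration areas or households does not reduce it.

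The stated inputs treat the enumeration area as if it were the allocated unit. Two consequences follow if district trends vary. A null regional result would be read against a power figure that the design does not have. A positive one could be false, because a model without a district term gives standard errors that are too small. Child survival is the stated impact hypothesis, alongside the primary implementation hypothesis on the pace of CHPS coverage, and the results are meant to inform national policy.

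**Working it through.** **Reproducing the 80%.** This cannot be done. The article gives no baseline mortality, ICC value, children or households per cluster, regional split of the 247 clusters, sidedness or between-district variance. The check therefore grants the stated power in full at enumeration-area level and asks what is left once districts are allowed to vary.

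**Inputs.** From the article: 15% reduction, 80% power, 5% level, 3 v 4 districts per region. Assumed: a two-sided test, and k, the between-district SD of the change in log mortality, over a range.

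**Step 1: standard error implied by the claim.** The effect is −ln 0.85 = 0.1625. For 80% power at two-sided 5%, SE₀ = 0.1625/(1.960 + 0.842) = 0.0580, so SE₀² = 0.003365.

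**Step 2: add the district component.** SE² = SE₀² + k²(1/3 + 1/4) = 0.003365 + 0.5833k². At k = 0.10, for example, SE² = 0.003365 + 0.005833 = 0.009198, SE = 0.0959, and effect/SE = 1.69.

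**Step 3: power and error.** Normal power is Φ(0.1625/SE − 1.960). The t version uses the noncentral t with 3 + 4 − 2 = 5 df (critical value 2.571). If the analysis keeps SE₀ and ignores districts, its true type I error is 2[1 − Φ(1.960·SE₀/SE)].

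| k | SE | Power, normal | Power, t 5 df | Type I error if districts ignored |
|---|---|---|---|---|
| 0 | 0.0580 | 80% | 61% | 5% |
| 0.03 | 0.0624 | 74% | 56% | 7% |
| 0.05 | 0.0695 | 65% | 47% | 10% |
| 0.10 | 0.0959 | 40% | 28% | 24% |

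The reduction detectable with 80% power on 5 df is 22% at k = 0.05, 29% at 0.10 and 36% at 0.15.

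**Step 4: ceiling with unlimited children.** Setting SE₀ = 0 leaves SE = k√(7/12). Power on 5 df is then above 99% at k = 0.03, 92% at 0.05, 41% at 0.10 and 21% at 0.15. It reaches 80% only if k is about 0.06 or less.

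**Step 5: sidedness.** A one-sided 5% test treated the same way gives 69% at k = 0 and 40% at k = 0.10 on 5 df.

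**Step 6: single contrast or interaction.** The article does not say which was sized. If it was a single contrast, and if the sampling variance doubled for the interaction, power at k = 0 would be 51% (normal) or 36% (5 df). Doubling is the case without clustering. Reusing the same enumeration areas removes their stable component of variance, so the true factor depends on inputs that are not given.

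**Step 7: pooling the regions.** With 6 v 8 districts, SE² = SE₀²/2 + k²(1/6 + 1/8). On 10 df, power is about 95%, 85% and 58% at k = 0, 0.05 and 0.10.

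**The case against.** The strongest reply is that nothing here shows that the survey lacks 80% power. The article omits the numbers needed to test the claim. At exactly zero district variance the planned enumeration-area analysis keeps its 80%, and the 61% in the table is then only the price of a 5-df test. This stands. A reader might infer that the stated power is proven not to be delivered, but the document does not support that.

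Second, a condensed article may leave to the full protocol whether the interaction was sized, and reusing enumeration areas helps the difference-in-differences. This also stands, so step 6 is conditional and is not a demonstrated doubling of variance.

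Third, one might try to show the shortfall from enumeration-area figures alone. That is fragile. Under an assumed ICC of 0.01 and about 62 clusters per region-arm (247/4, itself assuming equal regions), the power ceiling for a single-round contrast with unlimited children is 59% at an assumed mortality of 60 per 1000 but 86% at 110 per 1000. A worked example with an assumed 60 children per cluster, 80 deaths per 1000 and k = 0.10 gives 16% power per region and 32% pooled. At zero district variance it already gives 20% and 43%, so it mostly reflects the assumed cluster size. Neither calculation is relied on here.

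Fourth, differential timing of cluster exposure might add information within districts. It could add some, but S in equation (1) is defined as treatment area against comparison area, so the model as written does not use it.

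None of these replies supplies a district-level term in the sizing or the model.

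**Conclusion.** The claim of 80% power at the 5% level in each region is not supported by the design described, because the sizing and the model stop at the enumeration area while intervention is by district. The size of the loss is unknown from the document. A between-district SD of 0.03 in the log change already takes 6 points off the normal-theory power (80% to 74%), and an SD of 0.10 halves it (to 40%). On 5 df the corresponding figures are 56% and 28%. These results assume a two-sided test, enumeration-area power of exactly 80%, and district changes that vary independently with a common SD. Under the same assumptions, leaving districts out of the analysis keeps the apparent power only by giving up the nominal 5% level.

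A reader might also conclude that the pooled estimate must become the confirmatory one. That does not follow: separate regional effects are a stated aim, and choosing between the two is a trade-off for the investigators.

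**What to change.** - Withdraw the per-region power statement, or restate it by recomputing power and the minimum detectable reduction for the district-level difference-in-differences with 3 v 4 districts, over a stated and justified range of the SD of district change.
- Report the inputs with it: baseline mortality, ICC, children per cluster, clusters per region, sidedness, and whether the interaction or a single contrast was sized.
- Allow for district variation in the analysis, through a district-by-period term in equation (1) or small-sample inference at district level, so that the 5% level holds.
- Report the pooled 6 v 8 district estimate and its power beside the regional ones, without requiring it to become the confirmatory contrast.

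The cost is a less favourable stated figure and wider intervals. No extra clusters, households or fieldwork are needed.

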#### Sample design

The sampling frame for the first stage was from the 2010 Population and Housing Census which provided a complete listing of Enumeration areas in the fourteen districts to be surveyed. The sampling frame contained information such as the location and estimated number of households. In each region, Enumeration areas were stratified by rural versus urban and by the estimated number of households in the cluster. Clusters were stratified into three groups (small, medium, or large yielding a total of 6 strata in each district. Enumeration areas were sampled from each stratum using probability proportional to population size (PPS). Weights will be applied at the cluster level to standardize probabilities of household selection based on the relative population size of clusters.

To obtain a sampling frame for the second-stage sampling, a household listing of all households in each cluster was compiled based on census information on household size and number women of reproductive age (15–49) in each household. Households were then stratified into three strata defined by the number of eligible women in each household.

To maximize sample efficiency for difference-in-difference estimation at the endline, baseline sample clusters will be reused without modification to permit longitudinal observation of clusters and the assessment of the average treatment effect arising from the timing of exposure of clusters to project interventions. The second-stage sampling procedure will be repeated, yielding a household sample for the longitudinal observation of children exposed versus unexposed to interventions over the duration of the project, with provision for statistical adjustment of baseline and endline differentials and changes in project endpoints that are unrelated to CHPS+ interventions.

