**Methods:**

A mixed method evaluation strategy has been launched involving: i) baseline and endline randomized sample surveys with 247 clusters dispersed in 14 districts of the Northern and Volta Regions to assess the difference in difference effect of stepped wedge differential cluster exposure to CHPS+ activities on childhood survival, ii) a monitoring system to assess the association of changes in service system readiness with CHPS+ interventions, and iii) a program of qualitative systems appraisal to gauge stakeholder perceptions of systems problems, reactions to interventions, and perceptions of change. Integrated survey and monitoring data will permit multi-level longitudinal models of impact; longitudinal QSA data will provide data on the implementation process.

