## Methods/design

### Hypotheses and goals

CHPS+ will test the primary implementation hypothesis that the pace of expansion of CHPS population coverage can be significantly increased relative to the pace of CHPS expansion in districts not yet exposed to CHPS+ interventions. Research is also designed to test the impact hypothesis that CHPS+ implementation will improve infant and child survival. A three component mixed method evaluation strategy has been launched for program evaluation involving: i) baseline and endline randomized cluster sample survey research with 247 census enumeration clusters dispersed in 14 districts of the Northern and Volta Regions for assessing the effect of cluster exposure to CHPS+ activities on childhood survival; ii) a service delivery point monitoring system for assessing the association of changes in service system readiness with CHPS+ interventions; and iii) a program of qualitative systems appraisal (QSA) to gauge stakeholder perceptions of systems problems, reactions to CHPS+ interventions, and perceptions of change. Temporal variance in project implementation will be monitored to provide stepped wedge recorded differential exposure to operations. Integrated survey and M&E data will permit multi-level longitudinal models of impact; longitudinal QSA data will provide data on the implementation process.

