#### Assessing impact

CHPS+ will have core, intermediate outcome, and process endpoints, each requiring systems of data capture, data management, and analysis to gauge project impact. These core endpoints and indicators will be consistent with the Ghana Ministry of Health core indicators of health improvement with instruments designed to maximize comparability with national Ghana Demographic and Health Survey instruments. This will involve indicators of under-five mortality, infant mortality, and neonatal mortality by gender of child; age specific and total fertility rates and proximate determinants that are relevant to policy; and indicators of parental health seeking behavior, such as skilled attendant delivery, care of sick children, exposure to community-based services, distance to health facility and utilization of facilities for essential care. Critical covariates essential to the understanding of equity and impact, such as educational attainment, household economic status, and distance to service point will also be assessed.

CHPS+ will utilize impact assessment strategies that have worked well for GEHIP. Routine compilation of time trends indicators will be supplemented with end-of-project *difference-in-differences* calculations for each indicator. This econometric strategy has been applied elsewhere for the assessment of non-randomized plausibility trials [44–46] and successfully applied to the evaluation of GEHIP [47]. The procedures involve collecting data in baseline clusters, monitoring systems changes and the timing of these changes, and repeating the survey in baseline clusters with a separate endline stage two sample to gauge effects. Regression analysis is based on merged baseline and endline data for the estimation of parameters that control for baseline differences and contextual confounders, changes over time that are unrelated to interventions, and conditional effects of interventions that control for these confounding changes by estimating net intervention effects. A difference-in-difference estimate of program effects is given by the child survival effect of CHPS+ systems interventions (**S**) where individual child i is scored 1 if the household is located in a cluster that is exposed to CHPS treatment and zero otherwise and z is scored 1 if the case *i* is observed in the endline and zero if the case is observed in the baseline. If all covariates are equal to zero for child *i*, (*i.e.,*
*X*_*1*_*=**0*, *X*_*2*_*=**0,...*

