*X*_*k*_*=**0,*
*S=0,*
*Z=0*), the underlying mortality hazard is *h*_0_(t) and the conditional multilevel proportional hazard model is:1$$ {\boldsymbol{h}}_{x\sim SZ}\left(\boldsymbol{t}\right)={\boldsymbol{h}}_{\mathbf{0}}\left(\boldsymbol{t}\right){\boldsymbol{e}}^{\left[{\beta}_0+\sum \limits_{k=1}^K{\beta}_k{X}_{ij k}+\gamma {S}_j+\delta {Z}_{ij}+\zeta {S}_j{Z}_{ij}+{\mu}_j+{\varepsilon}_{ij}\right]} $$for all *t*, where:

*X̃*_*i*__*j*__*k*_ represents *K* characteristics of child *i* in cluster *j*;

*S*_*j*_ indicates whether cluster *j* is in the treatment area (*S* = 1) or comparison area (*S* = 0);

*Z*_*ij*_ indicates whether the person time of child *i* in cluster *j* occurs during the post-treatment period (*Z* = 1) or pre-treatment period (*Z* = 0);

*S*_*j*_*Z*_*ij*_ is a cross-level interaction term of treatment and period for estimating the net effect of treatment in the difference-in-differences approach;

and

*μ*, *ε* represent residuals for cluster and individual levels, respectively.

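### A stepped-wedge effect of exposure timing is promised, but the only written impact model has no exposure-time term and defines its period indicator in two incompatible ways

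*Protocol article*

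**What the plan says.** Three places promise an effect that depends on when clusters are reached. The abstract (Methods) announces the "difference in difference effect of stepped wedge differential cluster exposure to CHPS+ activities on childhood survival". *Hypotheses and goals* says: "Temporal variance in project implementation will be monitored to provide stepped wedge recorded differential exposure to operations". *Sample design* gives as a purpose of re-using the clusters "the assessment of the average treatment effect arising from the timing of exposure of clusters to project interventions". *Assessing impact* lists among the procedures "monitoring systems changes and the timing of these changes, and repeating the survey in baseline clusters".

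*Impact research: The household survey* describes a parallel layout. Eight districts receive the intervention and another eight "are being used as comparison districts"; fourteen of the sixteen are surveyed, at baseline and endline. No order or schedule of rollout is given.

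*Assessing impact* then writes the model:
- **S, in the text:** 1 "if the household is located in a cluster that is exposed to CHPS treatment and zero otherwise". Under Equation 1, S_j marks treatment area against comparison area.
- **Z, in the text:** 1 if the case is "observed in the endline and zero if the case is observed in the baseline". Under Equation 1, Z_ij is 1 if the child's person-time falls after treatment and 0 if it falls before.
- **Effect:** the product S_jZ_ij "is a cross-level interaction term of treatment and period", with coefficient zeta.

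**The concern.** A stepped-wedge analysis draws on clusters crossing over at different, known times, and needs exposure to vary over time within a cluster, separately from calendar time. Equation 1 is a two-by-two difference-in-differences. S does not change over time, Z has two levels, and no term carries start date, step, duration or calendar year.

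This matters because the intervention is built to arrive gradually. Under *Systems learning districts*, implementation begins in one or two localities of a participating district and spreads through exchanges and demonstration zones. Whether a cluster reached early and one reached late are coded alike depends on which definition of Z is used, and the article supplies two. At stake are what zeta estimates, how far it is pulled from the full-exposure effect, and whether readers credit the study with a design feature that it lacks.

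**Working it through.** **1. Promise against model.** The promise is an average effect arising from exposure timing. The terms of Equation 1 are covariates, S_j, Z_ij, S_jZ_ij, a cluster residual and an individual residual. The only term that could carry timing is Z, so everything turns on its definition.

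**2. The two definitions of Z.**
- *By survey round.* All endline observations have Z = 1. In treatment areas S·Z = 1 for all of them, including person-time before the cluster was reached. Early and late clusters share one code, and zeta averages exposed and unexposed time.
- *By post-treatment person-time.* Z may switch at a cluster's own start. No rule for the date is given, and a comparison cluster has no start of treatment. The analyst must invent a date for that arm.

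A given analysis uses one definition, so the consequences in steps 4 and 5 cannot both apply.

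**3. The article's own figure.** It states 80% power at the 5% level for a 15% reduction in under-five mortality in each region. This cannot be reproduced: baseline mortality, intra-cluster correlation, children per woman, households per cluster and clusters per region are not given. The 80% is therefore taken as stated.

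**4. Survey-round coding: dilution (illustration).** Assumptions: 15% is the effect under full exposure; the test is two-sided (sidedness is not stated); the standard error is whatever gives 80% power at hazard ratio (HR) 0.85; a share f of treatment-area endline person-time is truly exposed.
- Fitted HR ≈ 0.85f + (1 − f) = 1 − 0.15f.
- Power = Φ(2.80 × ln HR / ln 0.85 − 1.96), where 2.80 = 1.96 + 0.84.
- Event inflation = (ln 0.85 / ln HR)².

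| f | HR | Power | Events needed |
|---|---|---|---|
| 1.0 | 0.850 | 80% | 1.00× |
| 0.9 | 0.865 | 71% | 1.26× |
| 0.75 | 0.888 | 54% | 1.85× |
| 0.6 | 0.910 | 37% | 2.97× |
| 0.5 | 0.925 | 27% | 4.35× |

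For f = 0.5: ln 0.925 / ln 0.85 = 0.0780 / 0.1625 = 0.480; 2.80 × 0.480 − 1.96 = −0.62; Φ = 0.27.

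If starts are spread evenly over the first s years of an assumed five-year post-period, the mean start is s/2 and f = 1 − s/10. So s = 1 gives 0.9, s = 4 gives 0.6 and s = 5 gives 0.5. The article gives neither s nor f.

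**5. Person-time coding: drift (direction of reasoning only).** Let the log hazard fall by r a year in both arms, and let D be the gap between the mean calendar dates of post and pre person-time in an arm. The spurious part of zeta is −r × (D_treatment − D_comparison). It vanishes when both arms use the same observation window and the same switch date. Different dates do not guarantee bias: with evenly spread person-time over one shared window of length T and a single date c per arm, D = (c + T)/2 − c/2 = T/2 whatever c is. With unequal windows, or dates that vary within an arm, D can differ. The article fixes neither dates nor windows and gives no r, so no size or sign can be derived.

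**The case against.** The strongest reply is that Equation 1 is not blind to time. Z_ij is indexed by child and cluster and, under the equation, is defined on person-time, so S_jZ_ij could switch at each cluster's start and zeta would then average over post-treatment time. A reader might infer that the model contains no timing at all, or that the promised effect cannot come from it. The documents do not support either inference. What stands is that no start-date rule is given, the text just before the equation contradicts this reading, and it leaves comparison clusters without a date.

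A reader might also infer that the recorded dates go unused. That is not shown. *Hypotheses and goals* foresees multi-level longitudinal models on linked survey and monitoring data, *Quantitative systems monitoring* uses milestone dates to follow the pace of implementation, and the analysis plan is not at hand. Nor can one say that parallel trends will never be checked: compilation of time trends is planned, and such checks commonly sit in an analysis plan. Equation 1 itself offers no such check.

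The article also places its method among non-randomised plausibility trials, so the lack of randomisation is not hidden. And 15% may already be an area-level target that allows for partial exposure, since the predecessor programme reported a 49% reduction. In that case the power loss shown above does not arise.

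None of this removes the mismatch. The article itself states the target and fixes the equation, and the two are not tied together.

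**Conclusion.** The point holds as an inconsistency that should be corrected. A timing-based stepped-wedge effect is promised; the one specified impact model has no cluster-specific exposure-time term; the design is a parallel, non-randomised before-after comparison; and Z has two incompatible definitions. This follows from the text and needs no assumption.

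The size does not follow from the text. The HR range of 0.865 to 0.925 and the power range of 71% to 27% depend on an assumed exposed share of 0.9 to 0.5 and on reading 15% as a full-exposure effect. They apply only under survey-round coding. Drift applies only under person-time coding with dates that differ between arms, and cannot be quantified here. Adding the two together, or treating either as established, would go beyond the documents.

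**What to change.** - Define Z once, on calendar person-time, with one switch date common to both arms, and use that definition in both the text and the equation.
- Describe the design as a non-randomised controlled before-after (difference-in-differences) study with staggered exposure, in place of the stepped-wedge wording.
- Keep the assigned-area estimate from Equation 1, stating that it averages over treatment-area time not yet exposed.
- Add the same hazard model with a time-varying exposure term that switches on at the recorded start date, calendar-year effects in place of the single Z, and comparison person-time at zero exposure.
- Optionally, add pre-exposure year-by-S terms from the birth histories as a trend check.

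The cost is wording, analysis code and a rule linking each survey cluster to a recorded start date; the timing is already to be recorded. The added model has more nuisance parameters and slightly wider intervals. Exposure timing may also be confounded, because invitees to the exchanges are prioritised by past commitment to the programme. That is why the assigned-area estimate should stay alongside it.
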